## Abstract

**Introduction:**

Clear definitions are essential in science, particularly in the study of abstract phenomena like creativity. Due to its inherent complexity and domain-specific nature, the study of creativity has been complicated, as evidenced by the various definitions used to describe it and the multitude of tools which claim to measure it. Surgery is a safety-critical profession where creativity could be useful in navigating unforeseen problems and circumstances, as well as developing new innovations to improve patient outcomes. To validly and reliably study creativity in surgery, a surgery-specific definition is required. We aim to develop a consensus definition of creativity in surgery, utilizing the existing creativity literature and surgeon input.

**Methods and analysis:**

The objective of this study is to generate a consensus definition of creativity in surgery. We will first conduct a focus group comprised of 4–12 highly experienced surgeons to generate knowledge on surgeons’ perceptions, attitudes and beliefs about creativity in surgery, collect real-world examples of creativity in surgery, and obtain opinions on the existing definitions of creativity in the literature. The selection of focus group participants will be performed using purposive sampling of the chairs and/or chiefs of each surgical sub-specialty at our home institution. Several questions relating to creativity in surgery will be posed to the focus group, to be rated using a 7-point Likert scale and used as prompts for group discussion. We will also search MEDLINE, PsycINFO and EMBASE to find definitions of creativity in the scientific literature. Six definitions, chosen based on citation frequency and relevancy to surgery, will be presented to the focus group for ranking and discussion. Lastly, in addition to novelty and effectiveness, which are widely accepted as necessary components of creativity, the focus group will be asked to consider the necessity of other components for creativity in surgery, sourced from the scientific literature. Descriptive and thematic analyses are planned for the quantitative and qualitative data, respectively. The results of the focus group will be incorporated in the drafting of five definitions of creativity in surgery, which will be presented as initial Delphi statements in the Delphi study. For the Delphi panel, we will perform non-probability purposive sampling of surgeons and surgeon trainees at our home institution, with a minimum panel size of 12. Panellists will be asked to select the definition of creativity most relevant to surgery, with each Delphi round electronically delivered. After each round, the steering committee will meet to review the results and adjust the statements for the next round based on the feedback. A maximum of 5 rounds will be performed, or until consensus is reached (≥75% agreement). Recruitment is scheduled to begin on 1 August 2024.

**Ethics and dissemination:**

All focus group and panellists will be given written and verbal information on the study and provide signed, informed consent. We plan to publish the results of our study in a creativity science- or surgery-focused journal to disseminate the results of our study to relevant stakeholders. We also plan to present the results of our research at local, national, and international conferences.

## Introduction

Clear definitions are essential in science, particularly in the study of abstract phenomena: they facilitate the replication of studies and provide the conceptual foundation that directs the measurement of the construct and subsequent interpretation of results. Without them, we risk developing theorems that squander the full meaning of our findings [1].

Creativity is a complex construct which has been studied from a variety of perspectives [2–8]. This complexity has complicated the understanding of creativity–it is simply too multifaceted for a generalized model to be effectively applied. Of the countless definitions of creativity put forth in the literature [9, 10], two essential components–originality and effectiveness–have come to be widely accepted as essential to creativity [11, 12]. While this characterization is useful, and admittedly generalizable, its laxness permits substantial heterogeneity in scientific approach, as evidenced by the proliferation of ‘creativity tests’ which have been found to have limited theoretical correlation and validity [13–15]. Moreover, such a definition of creativity does not consider the contextual nature which dictates the originality and effectiveness of a given idea. For example, something novel and effective in the field of computer science may be ordinary and have little use in the field of psychology. Thus, a domain-specific approach is scientifically and practically important to understanding the process and products of creativity [16].

Surgery is a unique and safety-critical profession. This safety-critical nature is reflected in its standardized practices, protocols and training processes: through such standardization, variability in outcomes is reduced among surgeons and among patients, minimizing risk [17–20]. This standardization seems diametrically opposed to creativity, which has been associated with risk-taking [21–24]. Yet, creativity is useful, and often necessary, in high-risk, time-pressured situations, particularly when unforeseen problems arise: just consider the Apollo 13 mission, or the Mann-Gulch fire [25, 26]. Creativity in safety-critical situations can save lives–it follows that surgeons may also need the capacity to generate creative solutions to unforeseen issues.

Surgeons require a constellation of skills, including technical ability, communication, teamwork, decision-making, and leadership [27, 28]. Many of these skills are unique to the profession and likely interact with the necessary resources required for creativity–intelligence, knowledge, personality, motivation, and environmental factors–to constitute a surgeon’s creative potential [7]. If we are to validly measure the creative potential of surgeons and evaluate the products of creativity in the surgical context, a surgery-specific definition, reflecting the characteristics and competencies required for creativity in surgery as well as the contextual features of the profession, is essential. This definition will be particularly useful to creativity psychologists and surgical researchers looking to validly study the process of creativity in surgery and its implications for surgeons, their patients, and the healthcare system at large. With no such definition existing, we aim to generate a consensus definition of creativity in surgery using both the existing creativity literature and expert surgeon opinion.

## Methods and analysis

### Study purpose

The purpose of this study is to develop a consensus definition of creativity in surgery. The definition will provide the theoretical foundation from which creativity research in surgery can be conducted, facilitating its operationalization. In addition to developing a definition, we aim to characterize the creative surgeon and elucidate the relevance and importance of creativity in surgery.

### Study design

We plan to conduct a focus group, followed by a Delphi panel. Focus groups are a useful methodology for obtaining knowledge, perspectives, and explanations on a specific topic, and are particularly useful when existing knowledge is limited [29, 30]. Delphi studies use the Delphi method, which consists of iterative rounds of standardized surveys on a selection of anonymized panelists to achieve expert-based judgement on a given topic [31–33]. In addition to its use in the health sciences for developing standards or guidelines, measurement tools, and recommendations for action [32], the Delphi method has been utilized on several occasions to develop consensus definitions for terms lacking a clear or agreed-upon description [34–41]. Thus, the focus group and Delphi panel methodologies are suitable approaches for generating knowledge of creativity in surgery, which is limited, and developing a consensus definition of creativity in surgery.

### Steering group

A steering group will be constructed, consisting of at least 6 members. Each group member will possess extensive experience and training in health research methods, creativity research, statistics, and/or surgery. This multidisciplinary team will work together to conduct literature reviews, develop the Delphi content, and execute the study.

### Literature search

To identify the existing definitions of creativity in the literature, we will perform a systematic scoping review of the peer-reviewed literature on the MEDLINE, PsycINFO and EMBASE databases. We have developed a search strategy involving a combination of subject headings and search terms; the full search strategy is provided in S1 File. Title and abstract screening, full-text review, and data extraction will be performed independently and in duplicate, with discrepancies resolved by discussion until a consensus is reached. Upon completion of the full-text review, we will search the references of included papers for additional definitions.

### Expert focus group

We will begin by conducting a focus group comprised of highly experienced surgeons (10+ years of surgical experience), selected through non-probability purposive sampling of the chairs and/or chiefs of each surgical sub-specialty in the Department of Surgery at our home institution. We will seek to recruit between 4–12 focus group participants, in line with existing qualitative research guidance [42, 43]. Basic demographic characteristics (i.e., age; sex) and information on the focus group participants’ surgical experience (i.e., years of surgical experience; specialty) will be collected. The objective of the focus group will be to collect preliminary data on surgeons’ perceptions, attitudes and beliefs about creativity in surgery, collect real-world examples of creativity in surgery, and obtain expert opinions on the existing definitions of creativity in the literature. The data from the focus group will aid the construction of the initial definition statements used in the Delphi study. Given our objective of developing of definition generalizable to the entire domain of surgery, efforts will be made to construct a focus group from a range of surgical sub-specialties.

We developed a semi-structured topic guide to guide the focus group discussions. The guide will be integrated into Slido, a PowerPoint software add-on which facilitates live polling of audiences during presentations [44]. The following questions will be proposed to the focus group, to be rated via a 7-point Likert scale: ‘How important is creativity in surgery?’; ‘I have confidence in my ability to solve problems creatively’; ‘My work in surgery makes me more creative’; and ‘How important is surgical experience in the ability to be creative?’. Responses will be anonymized to reduce dominance and group conformity [31]. Once the focus group has submitted their responses, the results will be presented and used as a starting point for discussion, allowing the surgeons to elaborate on their responses.

We plan to explore the characteristics of a creative surgeon, posing the following question to the focus group: ‘What abilities or traits are required for a surgeon to be creative?’. The question will be an open text field, with multiple responses permitted. Once the focus group has submitted their responses, the results will be presented for further discussion. An open discussion on examples of creativity, inside and outside of the operating room, will also be had to collect real-world examples of creativity in surgery.

Using the existing literature, we identified 6 criteria which, in addition to novelty and effectiveness, have been considered key components of creativity: aesthetic, surprising, ethical, influential, authentic, and predictable [15, 45–49]. The focus group will be asked to select as many or none of the proposed criteria to add to the standard definition of creativity [11], to be considered as necessary components of creativity in surgery. A discussion period will follow to allow the focus group to expand on their responses.

Lastly, based on the results of our literature search, we will provide a list of existing definitions of creativity in the scientific literature, chosen by frequency of citation and relevancy to the profession as determined by the steering committee. The focus group will be asked to anonymously select the definition that is most relevant to the surgery. After all responses have been logged, the results will be presented and discussed.

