### Analysis of focus group discussions

The responses to the Likert-measured questions will be descriptively analyzed and presented as medians, with interquartile ranges. Graphic representation of the data will be generated, where appropriate. Additionally, the discussions will be audio-recorded and transcribed verbatim. The primary researcher will perform a thematic analysis of the data, with the following process performed: active reading of the data; generation of the initial codes; theme identification; reviewing and categorization of themes; defining and finalizing themes; and reporting the findings [50]. We will perform the analysis utilizing a post-positivist approach, with the aim of maintaining the objectivity of the codes and minimizing researcher bias [51]. Reflexivity and establishment of structural coherence between the data and the interpretations will be practiced to maximize the trustworthiness of the results [52].

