### Delphi administration

The Delphi method will be conducted in the following fashion:

Round 1 –We will collect data on the panelists’ surgical specialty and years of surgical experience, as well as their perceived importance of creativity in surgery (7-point Likert) and its effect of the surgical profession on their creativity (7-point Likert). The panellists will then be presented with the five drafted definitions of creativity in surgery, choice-randomized, and asked to rank the definitions. An open-text field will allow panellists to suggest changes to the presented definitions.

Round 2–5 –If a consensus was not achieved after the first round, up to 5 rounds will be conducted. The suggested changes from the open-text field may be used to make alterations to the definitions. Following the presentation of the previous round’s results, the panellists will be asked to re-rank the definitions.

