### Definition of consensus

The primary outcome of interest will be consensus on the definition of creativity in surgery. Research on Delphi studies has identified 75% agreement as the median threshold [54, 55]. This will be the *a priori* set threshold for this study. In the case that consensus on a definition is not reached, we will report the results of each round, explore reasons for the lack of consensus, and narratively discuss the implications of the findings on the understanding of creativity in surgery.

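### The focus group item on surgery's effect on creativity names only the positive direction, so its rating cannot separate 'no effect' from 'less creative' (minor)

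*Protocol article*

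**What the plan says.** All references are to the protocol article.

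- **Expert focus group.** Four items are listed, "to be rated via a 7-point Likert scale". Two are questions about importance and two are first-person statements. One of the statements is "My work in surgery makes me more creative". The scale's anchors are not given. Answers are anonymous, with the stated reason of limiting dominance and conformity. They are then shown to the group and "used as a starting point for discussion, allowing the surgeons to elaborate on their responses".
- **Analysis of focus group discussions.** "The responses to the Likert-measured questions will be descriptively analyzed and presented as medians, with interquartile ranges". In addition, "the discussions will be audio-recorded and transcribed verbatim", and a thematic analysis follows.
- **Delphi administration, Round 1.** Panellists rate a related item, described as "its effect of the surgical profession on their creativity (7-point Likert". Its wording and anchors are not shown.
- **Study purpose.** Besides the definition, the study aims to characterise the creative surgeon and to clarify how relevant and important creativity is in surgery.
- **Definition of consensus.** "The primary outcome of interest will be consensus on the definition of creativity in surgery", with a threshold of 75% agreement.

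**The concern.** What is being measured is the effect of surgical work on the surgeon's own creativity. That effect has a natural zero and two directions. The statement offers one direction and asks for agreement with it. Disagreement then means only 'not more creative', which covers both 'unchanged' and 'less creative'.

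A negative answer is foreseeable. The Introduction remarks of standardised surgical practice that "This standardization seems diametrically opposed to creativity, which has been associated with risk-taking". If some chairs and chiefs hold that view about their own work, it would be useful to see it in the data.

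Two things are at stake. A low median could not be read as either 'no effect' or 'harmful effect'. A high median could owe something to a tendency to agree with a positively worded statement.

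**Working it through.** The plan attaches no sample size, error rate or power to this item, so there is no figure of its own to reproduce. The check is one of logic, with a small illustration.

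**Step 1: what each answer can mean.** Assume ordinary disagree-to-agree anchors on 1 to 7, with 4 as the middle.

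| Surgeon's view | Truthful response to the statement |
|---|---|
| Work makes me more creative | Agree (5 to 7) |
| Work has no effect | Disagree (1 to 3), or perhaps 4 |
| Work makes me less creative | Disagree (1 to 3) |

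The three points on the disagree side have no unique meaning. Some 'no effect' respondents may choose 4, but 4 can also mean 'undecided', and the reader of the results cannot tell which convention a respondent used.

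**Step 2: an illustration with 12 respondents**, the upper end of the planned group size. For simplicity, let agreement be scored 6 and disagreement 2 (assumed values).

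- Group A holds 4 'more', 4 'no effect' and 4 'less'. Ratings: 6 four times, 2 eight times (4 + 4).
- Group B holds 4 'more' and 8 'no effect'. Ratings: 6 four times, 2 eight times.

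Both groups give a median of 2 and an interquartile range of 2 to 6. The distributions are identical, although a third of Group A (4/12 = 33%) reports a reduction and nobody in Group B does.

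**Step 3: the same groups on a bipolar item** (1 = much less creative, 4 = no effect, 7 = much more creative), with 'less' scored 2, 'no effect' 4 and 'more' 6.

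| | Below 4 | At 4 | Above 4 | Median | Interquartile range |
|---|---|---|---|---|---|
| Group A | 4/12 = 33% | 4/12 = 33% | 4/12 = 33% | 4 | 2 to 6 |
| Group B | 0/12 = 0% | 8/12 = 67% | 4/12 = 33% | 4 | 4 to 6 |

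The groups now separate. The medians still coincide, which is why the percentages below, at and above the midpoint are needed beside the median.

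**Step 4: what the discussion adds.** A surgeon who disagreed can explain why, and the remark enters the transcript. To do so, that surgeon must speak openly before fellow chairs and chiefs from one department. The poll was made anonymous to avoid that pressure. The transcript also leaves the reported median and interquartile range as they were.

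**Step 5: the two phases side by side.** The focus group statement is directional. The Round 1 item is described by the neutral word 'effect'. If the Round 1 item is neutral, the two phases ask about nearly the same thing in non-equivalent ways. If it repeats the focus group statement, the ambiguity recurs there, where no discussion is described and the open-text field is for changes to the definitions. The article does not show which applies.

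**The case against.** The strongest reply is that the rating is a discussion prompt and not a stand-alone measure. Positively worded agreement statements are an ordinary Likert format. Participants can disagree, they can then say what they meant, and the discussion is recorded and analysed. No hypothesis or decision depends on the result.

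Much of this stands, and it rules out several stronger readings that a reader might infer:

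- *That the study cannot record a reduction in creativity.* It can: the low end of the scale is available and the discussion is analysed. What the rating cannot do is distinguish a reduction from no effect.
- *That the Introduction says surgical work lowers a surgeon's creativity.* It describes a tension between standardised practice and creativity, then argues that creativity is useful and often needed in high-risk situations. A personal negative effect is an inference from that passage.
- *That Delphi Round 1 has the same fault.* Its wording is not shown and its description is neutral. An article commonly leaves exact survey wording to the instrument, so no defect is shown there.
- *That the ambiguity is certain.* It depends on disagree-to-agree anchors. The statement form makes these likely, but the article does not state them.

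The reply does not remove the point about the numerical result. The median and interquartile range are to be presented as results in their own right, and the discussion clarifies them only for those willing to give up anonymity.

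**Conclusion.** The concern holds in a narrow form. Under the assumption of disagree-to-agree anchors, the focus group rating and its summary cannot separate 'no effect' from 'less creative', and the wording may invite agreement. The size of any such shift cannot be derived from the article.

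Severity is minor. The item is one of four descriptive ratings from 4 to 12 participants. It bears on the secondary aim concerning the creative surgeon and the relevance of creativity, and it does not enter the 75% consensus rule. Focus group data do inform the drafted definitions, but nothing in the article shows a route by which this rating would change one of them.

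**What to change.** Replace the statement in the topic guide with a neutral bipolar 7-point item:

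*What effect does your work in surgery have on your creativity?* 1 = makes me much less creative, 4 = no effect, 7 = makes me much more creative.

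Report the median and interquartile range together with the percentages below, at and above 4. Give the counts as well, since one respondent is 25% of a group of 4 (1/4) and about 8% of a group of 12 (1/12).

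Use the same item in Delphi Round 1, so that the focus group and panel results can be set side by side. This is for consistency and is not the correction of a shown error; if the Round 1 item already reads this way, nothing changes there.

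The cost is the rewording of one item in the topic guide and, if needed, its counterpart in the Round 1 survey. No item is added, so the planned limit of 2 minutes per Delphi round is not put at risk. A question form also fits the guide, where two of the four rated items are already questions.

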### Analysis of focus group discussions

The responses to the Likert-measured questions will be descriptively analyzed and presented as medians, with interquartile ranges. Graphic representation of the data will be generated, where appropriate. Additionally, the discussions will be audio-recorded and transcribed verbatim. The primary researcher will perform a thematic analysis of the data, with the following process performed: active reading of the data; generation of the initial codes; theme identification; reviewing and categorization of themes; defining and finalizing themes; and reporting the findings [50]. We will perform the analysis utilizing a post-positivist approach, with the aim of maintaining the objectivity of the codes and minimizing researcher bias [51]. Reflexivity and establishment of structural coherence between the data and the interpretations will be practiced to maximize the trustworthiness of the results [52].

